**5.1 Laboratory evaluation**

##### Humans

Human fecal analysis will be performed using the Kato-Katz thick smear technique (Katz et al 1972.), 2 stools will be collected per person and 3 slides will be prepared per stool. Each smear will be read blind from the previous and each stool will be read blind from the previous.

Fecal sample containers will be labeled with the PID, and the date of distribution. Participants will be instructed to deposit samples from their own feces, separated by at most three days, into each container and to return the container immediately to one of several collection points, where the sample will be stored at 4 °C. Fecal samples returned later than 48 hours after defecation will not be accepted and new containers will be issued. The slide preparation will occur 24 hours after receipt of stool sample.

The term “egg positive” for *S. japonicum* will be defined as a single egg found in any one of the 6 fecal thick smear slides. Cohort members found to be egg positive will be treated for ethical reasons.

Any cohort member who receives treatment whether it is as part of the annual mass treatment or as a direct result of being egg positive will have to provide stool samples as explained above 1 month after treatment to test the efficacy of that treatment.

Results of the fecal analysis will be recorded on the human stool examination forms shown in the appendix.

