**3.1 Study procedure**

##### Pre-Trial

A research team in each province will be established in order to carry out the fieldwork and the laboratory testing in their respective research institutes.

A sampling survey in Jiangxi Province will be done by early September 2004. The data from this survey will be distributed to the project investigators for the selection of the study villages.

Approximately 40-50 human faecal samples and 30 bovine faecal samples per village will be collected. Additionally, during the sampling survey, faecal examinations for sheep and goats (40-50 each species, hatching method) will be carried out to estimate their prevalence, as a variable for modelling.

Maps of the study sites will be prepared in order to show their location.

After the Jiangxi sampling survey, the study villages will be selected and matched according to the village selection criteria, by the project investigators. Within each pair, one village will be randomly selected as the intervention village thus leaving the other of the pair as the control.

A current list (census) of each village population by household will be constructed prior to baseline

**Stage 1:** October 2004

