##### Bovines

Bovine fecal analysis will be performed using the traditional Chinese miracidial hatching test and their sedimentation method. The miracidial hatching test will determine whether or not the bovine is positive or negative for *S. japonicum* and their sedimentation method will determine the intensity of infection.

One stool will be collected per animal with 3 hatches (50 g faeces/hatching), which are to be read blind from each other.

The stool is to be collected from the animals’ stable or directly from its rectum.

The research team will collect the stool for examination into containers labeled with the date of collection and the type of animal with its PID.

Any bovine which receives treatment whether it be as part of the twice annual mass treatment or as a direct result of being egg positive will have to have a stool sample collected 1 month after treatment to test the efficacy of that treatment.

Results of the fecal analysis will be recorded on the bovine stool examination forms shown in the appendix.

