##### Humans

Case Report Forms (CRF) CRFs will be kept for each subject, for each data collection, i.e.

human survey and human fecal examination. Subjects will be identified by their administrative

village, natural village, house identification, and an individual identification within the house. In

addition they will be assigned a unique serial number which will be constant over time, and

enable longitudinal analysis. CRFs will be completed according to standard operation procedures

(SOPs). That is, all data on the CRF will be legibly recorded in black ink, corrections may only

be made by striking through an incorrect entry with a single line and entering the correct

information adjacent to it. The correction will be initialed and dated by the investigator or a

designated, qualified individual.

A migration CRF will be used to record exit from the study, the date of exit, and the reason.

In-migrants will not be recruited to the study, however their entry to the village will be recorded along with the date of entry, and the reason. Furthermore, these in-migrants will be tested and treated on entry.

Note: Only those who enter the study site during the transmission season and stay longer than two weeks will be examined and treated. If from an endemic area or are having water contact, need to be examined and treated. If living in the village, need to be examined and treated. All will be recorded.

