**Investigator sign:**

**Date(yyyy/mm/dd):**

**FORM 2B Primary Human Stool Examination**

Year:

| **AID** | **NID** | **HID** | **PID** | **Slide Code**  **(from A to F)** | **Egg Count** | **Other helminths** |
| --- | --- | --- | --- | --- | --- | --- |
|  |  |  |  |  |  |  |
|  |  |  |  |  |  |  |
|  |  |  |  |  |  |  |
|  |  |  |  |  |  |  |
|  |  |  |  |  |  |  |
|  |  |  |  |  |  |  |
|  |  |  |  |  |  |  |
|  |  |  |  |  |  |  |
|  |  |  |  |  |  |  |
|  |  |  |  |  |  |  |
|  |  |  |  |  |  |  |
|  |  |  |  |  |  |  |
|  |  |  |  |  |  |  |
|  |  |  |  |  |  |  |
|  |  |  |  |  |  |  |
|  |  |  |  |  |  |  |
|  |  |  |  |  |  |  |
|  |  |  |  |  |  |  |
|  |  |  |  |  |  |  |
|  |  |  |  |  |  |  |
|  |  |  |  |  |  |  |
|  |  |  |  |  |  |  |
|  |  |  |  |  |  |  |
|  |  |  |  |  |  |  |
|  |  |  |  |  |  |  |
|  |  |  |  |  |  |  |
|  |  |  |  |  |  |  |
|  |  |  |  |  |  |  |
|  |  |  |  |  |  |  |
|  |  |  |  |  |  |  |
|  |  |  |  |  |  |  |
|  |  |  |  |  |  |  |
|  |  |  |  |  |  |  |
|  |  |  |  |  |  |  |
|  |  |  |  |  |  |  |
|  |  |  |  |  |  |  |
|  |  |  |  |  |  |  |
|  |  |  |  |  |  |  |

OTHER HELMINTHS: A= Ascaris, B=Trichuris, C=Hookworm, D=Other

Investigator(sign) :

Date:

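### Slide readers are not masked to village or arm: the stated blinding covers only a person's other slides, and the results form carries village IDs

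*Protocol*

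**What the plan says.** - **Reading rule, human slides** (Protocol 5.1, Humans): "Each smear will be read blind from the previous and each stool will be read blind from the previous".
- **Reading rule, bovine hatching tests** (5.1, Bovines): the three hatches from a stool "which are to be read blind from each other". These two are the only blinding statements in the protocol.
- **Where results go** (5.1, Humans): "Results of the fecal analysis will be recorded on the human stool examination forms shown in the appendix". The form for the annual examination is "FORM 2B Primary Human Stool Examination" in Appendix I. Its first columns are "AID | NID | HID | PID | Slide Code", followed by egg count. The slide code runs from A to F.
- **What the IDs mean** (Section 6, Records to be kept, Humans): subjects are identified by administrative "village, natural village, house identification, and an individual identification within the house". Form 2D spells out the same items.
- **Container label** (5.1, Humans): "Fecal sample containers will be labeled with the PID, and the date of distribution". No masked laboratory code is mentioned anywhere.
- **Staffing** (3.1, Pre-Trial): "A research team in each province will be established in order to carry out the fieldwork and the laboratory testing".
- **Link from village to arm** (3.1, Baseline Survey, Bovines): bovines are treated in intervention villages and only examined in control villages.
- **End-point and case definition** (7.1 and 5.1): the end-point is human infection rates, and a single egg on any one of 6 slides makes a person positive.

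**The concern.** The end-point depends on a person at a microscope finding an egg, and one egg decides case status. Detection of light infections therefore depends on reading effort. If the reader knows, or can work out, which village a slide comes from, expectation about the intervention can affect that effort by arm. The first study objective is to repeat the results of a pilot in which bovine treatment was followed by lower infection, so an expectation exists.

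A reading difference tied to arm is systematic. It does not shrink with 300 people per village or with 4 pairs, and the design effect of 1.5 in Section 7.3 covers similarity within clusters, not misclassification by arm. The same readings supply the egg-count intensity outcome (7.2) and feed the interim decision on early termination (3.1, Stage 8).

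**Working it through.** No figure in the protocol is in dispute, so there is none to reproduce. The check sets the texts side by side; the arithmetic only illustrates what would follow from assumed miss rates.

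**1. Scope of the blinding.** Both blinding statements concern specimens from the same person or animal. Neither mentions village, pair or allocation.

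**2. What the form exposes.** Form 2B puts village, house and person on the same row as the egg count. The code A to F separates the six slides of one person but cannot tell one person from another. Unless a further code exists that the protocol does not mention, a person identifier must accompany the slide or its row.

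**3. From village to arm.** Bovine treatment takes place in one village of each pair only. Anyone who knows the fieldwork can read the arm from the village ID.

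**4. Who might know.** One team per province is responsible for fieldwork and laboratory testing. This shows overlap at team level. It does not show that the same individuals do both.

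**5. Effect on the rate ratio.** Assume no true effect, infection rate p in both arms, and a share m of positive persons missed in intervention villages only.
- Observed ratio = p(1 − m)/p = 1 − m.
- m = 0.10 gives 0.90; m = 0.20 gives 0.80.

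**6. Effect on false positives.** Inputs from 7.3: 4 pairs, 300 per village, design effect 1.5, 20% attrition, 1% level in year 1 and 5% in year 2. Assumed: two-sided test, two-proportion normal approximation, p between 5% and 15% (Section 4.1 gives 10-15% at baseline; the follow-up rate is not given).
- Effective n per arm: 4 × 300 / 1.5 = 800 in year 1; 800 × 0.8 = 640 in year 2.
- With d = pm, s0 the pooled and s1 the unpooled standard error: rejection probability = Φ((d − z·s0)/s1) + Φ((−d − z·s0)/s1).
- Worked case, year 2, p = 0.10, m = 0.10: d = 0.01, s0 ≈ s1 ≈ 0.0164, z = 1.96. The terms are Φ(−1.35) ≈ 0.089 and Φ(−2.57) ≈ 0.005, in total about 9.4%.

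| Nominal level | m | p = 5% | p = 10% | p = 15% |
|---|---|---|---|---|
| 5% (year 2) | 0.10 | 7.0% | 9.4% | 12.0% |
| 5% (year 2) | 0.20 | 13.9% | 23.9% | 34.9% |
| 1% (year 1) | 0.10 | 1.9% | 3.0% | 4.3% |
| 1% (year 1) | 0.20 | 5.4% | 11.9% | 20.6% |

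With m = 0 the rates are the nominal 5% and 1%.

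**7. Slide-level against person-level misses.** Here m is per person. Someone with eggs on k slides is lost only if all k are missed. If misses are independent at rate s, that is s to the power k: s = 0.20 with k = 2 gives 0.04. The figures above therefore apply to slide-level misses of the same size only for people with a single positive slide.

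**The case against.** **Form 2B may not be used at the bench.** The protocol says results are recorded on it, not that the reader fills it in at the microscope. One row per slide fits later transcription equally well, and the container carries only the person ID and a date. A reader might infer that the form defeats the stated blinding between slides. The protocol does not support that; the most that can be said is that the form could undermine it if used at the bench. The objection does not touch the missing masking to village.

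**The team is not the individual.** A reader might infer that the people who treat the bovines also read the slides. The staffing sentence does not mention bovine treatment or assign both jobs to the same persons. This stands, but nothing in the protocol separates the roles either.

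**The miss rates are assumed.** This stands. No figure in the protocol supports 10% or 20%, and the six-slide rule dilutes slide-level misses in people with several positive slides.

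**There are safeguards.** Section 4.1 requires both villages of a pair to lie in one province, so one provincial team tests both arms and differences between laboratories are not confounded with arm within pairs. Every positive is to be treated, which gives readers a reason not to under-read. Both points are fair. The first does not remove knowledge of arm. The second applies in both arms and does not rule out a difference between them.

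**Comparison with the planned effect.** It is tempting to call a 10-20% bias a large share of a planned 42% reduction (0.60 × 0.70, from the first row of the power table). The table lists effect size and coverage but never says that their product is the reduction in human infection. Nor does one constant effect fit that row. Year 1 power of 26.7% at two-sided 1% implies a shift of 2.576 − 0.622 = 1.954. After 20% attrition this is 1.954 × √0.8 ≈ 1.75, which gives Φ(1.75 − 1.96) ≈ 42% power at 5%, not the stated 80.3%. The benchmark should not be used.

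**An analysis plan could cover it.** Masking of readers is a matter of laboratory conduct that Section 5.1 itself addresses, and only in part. It is not something left to a statistical analysis plan.

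**Conclusion.** The point holds as an exposure to bias that the protocol's own reading rule leaves open. Section 5.1 masks readers to a person's previous smear and stool and to nothing else. The prescribed form carries village IDs, a village ID can reveal the arm, and fieldwork and laboratory testing belong to the same provincial team. A visual end-point decided by one egg is thereby open to differential reading by arm.

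A reader might go further and conclude that the readings will be biased. The protocol does not show that, and it gives no basis for a size. The ratios of 0.90 and 0.80 and the inflated error rates rest on assumed person-level miss rates in intervention villages only, no true effect, and a simple two-proportion test at the planning sample size. They show that modest differential misreading would matter, not that it will occur. The change is worth making because it protects the trial end-point at low cost.

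**What to change.** 1. Add to 5.1 that slide readers are blind to village and allocation.
2. Label each slide with a random code only.
3. Give readers a version of Form 2B with slide code and egg count only (plus the other-helminths column if it is wanted), and link the code to AID, NID, HID and PID at data entry.
4. Where collection timing allows, read slides from the two villages of a pair in mixed order. The protocol does not say that stools from paired villages arrive together, and slides are prepared 24 hours after receipt, so this step should be conditional.

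Cost: relabelling and one linkage step for about 8 villages × 300 people × 6 slides = 14,400 slides per annual survey (more if cohorts exceed the minimum of 300, and more again if the one-month post-treatment stools are included), with some care over batching. No extra readers are needed. The same coding for the bovine hatching tests on Form 3C is optional, since bovine infection is not the trial end-point.

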##### Bovines

Bovine fecal analysis will be performed using the traditional Chinese miracidial hatching test and their sedimentation method. The miracidial hatching test will determine whether or not the bovine is positive or negative for *S. japonicum* and their sedimentation method will determine the intensity of infection.

One stool will be collected per animal with 3 hatches (50 g faeces/hatching), which are to be read blind from each other.

The stool is to be collected from the animals’ stable or directly from its rectum.

The research team will collect the stool for examination into containers labeled with the date of collection and the type of animal with its PID.

Any bovine which receives treatment whether it be as part of the twice annual mass treatment or as a direct result of being egg positive will have to have a stool sample collected 1 month after treatment to test the efficacy of that treatment.

Results of the fecal analysis will be recorded on the bovine stool examination forms shown in the appendix.

**5.2 Treatment Regime**

Humans

All village residents will be treated with an annual single dose of praziquantel (Pzq) 40mg/kg. Participants will be observed for 15 minutes after taking the medication.

Stool samples will be taken from sentinel cohort members 1 month after the treatment to determine the efficacy of treatment. Those found to be egg positive would be retreated with a single dose of Pzq 40 mg/kg. This process will be repeated until the subject is cured of infection.

Note: Previous studies in Poyang and Dongting Lakes show 85% efficacy on a single praziquantel dose, with 100% efficacy following re-examination and re-treatment as described above (Li et al, 1999).

Interloping fisherman and boatmen are to be treated twice annually if applicable and possible with Pzq 40mg/kg.

## Bovines

All bovines in the intervention villages will be treated twice annually with a single dose of praziquantel (Pzq) until cured. Buffaloes are to be treated with Pzq 25mg/kg and cattle are to be treated with Pzq 30mg/kg.

Stool samples will be taken 1 month after the treatment to determine the efficacy of treatment. Those found to be egg positive would be retreated with a single dose of Pzq (buffaloes 25mg/kg, cattle 30mg/kg). This process will be repeated until the animal is cured of infection.

All new bovines to the intervention village will be tested and treated as per the above regime and this will be recorded. Additionally newborn bovines will be recorded and treated 3 months after birth.

Neighbouring bovines found to be on the study sites’ marshland will be regarded as if they are part of the study group and hence will be treated accordingly. They will not be included in the calculation of prevalence.

Note: 100% treatment coverage must be achieved for the bovines.

Other mammals such as sheep and goats will also be treated twice annually in both control and intervention villages by single dose of 20 mg/kg. Moreover, if dogs and pigs are roaming on the marshland they too will be treated with Pzq 20mg/kg in both control and intervention villages.

# Adverse reactions

##### Humans

Treatment by praziquantel has been a routine, accepted, well-tolerated and widely used measure to control schistosome infection in all endemic areas of China. Treatment with praziquantel is safe, with very limited side effects. In the very unlikely event of minor side effects such as headache, medical treatment will be offered free of charge immediately. Participants in the project are at no greater risk than when they join the local schistosomiasis control program or see doctors in local clinics.

# Bovines

In the event of a bovine death because of the Pzq, the owner will be compensated for the loss.

**6.0 Data Collection**

- 1. **Records to be kept**

##### Humans

Case Report Forms (CRF) CRFs will be kept for each subject, for each data collection, i.e.

human survey and human fecal examination. Subjects will be identified by their administrative

village, natural village, house identification, and an individual identification within the house. In

addition they will be assigned a unique serial number which will be constant over time, and

enable longitudinal analysis. CRFs will be completed according to standard operation procedures

(SOPs). That is, all data on the CRF will be legibly recorded in black ink, corrections may only

be made by striking through an incorrect entry with a single line and entering the correct

information adjacent to it. The correction will be initialed and dated by the investigator or a

designated, qualified individual.

A migration CRF will be used to record exit from the study, the date of exit, and the reason.

In-migrants will not be recruited to the study, however their entry to the village will be recorded along with the date of entry, and the reason. Furthermore, these in-migrants will be tested and treated on entry.

Note: Only those who enter the study site during the transmission season and stay longer than two weeks will be examined and treated. If from an endemic area or are having water contact, need to be examined and treated. If living in the village, need to be examined and treated. All will be recorded.

##### Bovines

Case report forms will also be kept for the bovines. Their administrative village, natural village, house identification, host identification, animal type, sex and age will identify the bovines. In addition, they will be assigned a unique serial number, which will be constant over time, thus

enabling longitudinal analysis. A stool examination form will record the results of the fecal testing; a migration section will be included on the stool examination form and it will be used to record exit from the study, the date of exit, and the reason. In addition, it will be used to record entry into the study, the date of entry, and the reason. The recording of the bovine data will follow the same SOP as that of the recording of the human data.

- 1. **Data Management**

A database will be designed using Microsoft Access in order to manage the data. Each research team will double enter the data at their respective research institute. The CRFs used to enter the data from will be stored in a secure, fireproof place in case they need to be reused and to protect the identities of participants. It is important that the same procedure is used to enter the data and the same database is used across all research teams and their research institutes in order to standardize this process.

**Statistical Considerations**

**7.1 Outcome Measures**

The outcome measures for this study include the prevalences, infection and reinfection rates, intensities of infection and incidences. The end-point for the trial will be human infection rates. The efficacy of buffalo treatment will be measured by the accumulated comparison of human infection rates across intervention and control villages, and will be reflected in the predicted percentage of human infection-years prevented by the intervention. Human infection rates will be assessed at the end of each year for 4 years.

**7.2 Outcome Measure Formulae**

Prevalence = No. of egg positive cases

No. persons at risk × 100

For the prevalence per village, the number of persons at risk would equal the village population.

Incidence of infection : Since all positive cases are treated (and confirmed negative) at the end of

each year, the incidence rate of infection for a year is the number of infected persons in the cohort

found at the end of each year (having been present during the year), divided by the number of

persons in the cohort present during the period.

Year K Incidence density = No. of infections at end of year K _____ × 100

(K=2 to 5) No. of persons in cohort at end of years K and K-1

To take account of drop-outs, where additional information is available on the timing, we will be

able to refine this estimate by using a ‘person-time denominator’, which modifies his or her

exposure time by drop-out time: person-time = date of drop-out – date of start of period:

Incidence of newly-infected: This measure examines the rate of infection in those not infected at

the end of the previous period (year). It is the number of infected persons in the cohort found at

the end of each year (having been present during the year), divided by the number of persons in

the cohort present during the period, and negative at the end of the previous year.

Year K Newly-infected = No. of infections at end of year K__________ × 100

(K=2 to 5) No. of persons in cohort at end of

years K and K-1, and negative at end of year K-1

Rate of reinfection: This measure examines the rate of infection in those infected at the end of

the previous period (year). It is the number of infected persons in the cohort found at the end of

each year (having been present during the year), divided by the number of persons in the cohort

present during the period, and positive at the end of the previous year.

Year K Re-infected = No. of infections at end of year K × 100

(K=2 to 5) No. of persons in cohort at end of years K and K-1,

and positive at end of year K-1

Intensity of reinfection: The intensity of infection for new cases and the intensity of reinfection

will be determined by the number of eggs per gram of feces, which is measured using the Kato-Katz thick smear technique.

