### 2.0 Study Objectives

This study aims to achieve the following objectives.

1. Repeat the results obtained from the TMRC-supported pilot intervention study, regarding the hypothesis that “Bovine, especially buffalo, infections are responsible for the persistence of human schistosomiasis transmission in the marshlands and lake areas of China.” However on a larger and more generalizable scale.
2. Examine the efficacy of bovine chemotherapy on human infection and reinfection rates and how this gives insight into the use of a potential bovine vaccine.
3. Assess bovine chemotherapy as a plausible schistosomiasis control method, particularly in combination with human treatment.
4. Integrate the empirical data collected from the study into the previously TMRC-developed mathematical model.
5. **Study Procedure**

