**FORM 2C Primary Individuals For Treatment**

***Year:***

| **Name** | **AID** | **NID** | **HID** | **PID** | **TREATMENT? Y/N** | **REASON IF NO** |
| --- | --- | --- | --- | --- | --- | --- |
|  |  |  |  |  |  |  |
|  |  |  |  |  |  |  |
|  |  |  |  |  |  |  |
|  |  |  |  |  |  |  |
|  |  |  |  |  |  |  |
|  |  |  |  |  |  |  |
|  |  |  |  |  |  |  |
|  |  |  |  |  |  |  |
|  |  |  |  |  |  |  |
|  |  |  |  |  |  |  |
|  |  |  |  |  |  |  |
|  |  |  |  |  |  |  |
|  |  |  |  |  |  |  |
|  |  |  |  |  |  |  |
|  |  |  |  |  |  |  |
|  |  |  |  |  |  |  |
|  |  |  |  |  |  |  |
|  |  |  |  |  |  |  |
|  |  |  |  |  |  |  |
|  |  |  |  |  |  |  |
|  |  |  |  |  |  |  |
|  |  |  |  |  |  |  |
|  |  |  |  |  |  |  |
|  |  |  |  |  |  |  |
|  |  |  |  |  |  |  |
|  |  |  |  |  |  |  |
|  |  |  |  |  |  |  |
|  |  |  |  |  |  |  |
|  |  |  |  |  |  |  |
|  |  |  |  |  |  |  |
|  |  |  |  |  |  |  |
|  |  |  |  |  |  |  |
|  |  |  |  |  |  |  |
|  |  |  |  |  |  |  |
|  |  |  |  |  |  |  |
|  |  |  |  |  |  |  |

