**REASON IF NO:**

**1= refused exam; 2= work outside area; 3=pregnant; 4=death; 5=other**

**Investigator(sign) :**

**Date:**

# FORM 2D

# Follow-Up Human Stool Collection

**Name**

**Administrative Village id □□□**

# Natural Village id □□

**House id □□□**

**Individual id □□□□ (0001 – nth)**

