**Stool Number: ___(1 or 2)**

**Stool Specimen? □ (Y/N)**

**If Yes, Date collected stool: □□□□/□□/□□(yyyy/mm/dd)**

**If No, reason for no stool： □ (refused 1 not at home 2 sick 3 others 4)**

**FORM 2E**

**Follow-up Human Stool Examination:**

| **Date** | **ID** | **Slide** | **EPG** | **Other helminths** |
| --- | --- | --- | --- | --- |
|  |  |  |  |  |
|  |  |  |  |
|  |  |  |  |
|  |  |  |  |
|  |  |  |  |
|  |  |  |  |
|  |  |  |  |
|  |  |  |  |
|  |  |  |  |
|  |  |  |  |
|  |  |  |  |
|  |  |  |  |
|  |  |  |  |
|  |  |  |  |
|  |  |  |  |
|  |  |  |  |
|  |  |  |  |
|  |  |  |  |
|  |  |  |  |
|  |  |  |  |
|  |  |  |  |
|  |  |  |  |
|  |  |  |  |
|  |  |  |  |
|  |  |  |  |
|  |  |  |  |
|  |  |  |  |
|  |  |  |  |
|  |  |  |  |
|  |  |  |  |
|  |  |  |  |
|  |  |  |  |
|  |  |  |  |
|  |  |  |  |
|  |  |  |  |
|  |  |  |  |
|  |  |  |  |
|  |  |  |  |
|  |  |  |  |

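### The section 7.2 reinfection rate does not require that earlier positives were cleared, so a persistent infection counts as a reinfection and mildly dilutes this secondary comparison

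*Protocol*

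**What the plan says.** Protocol section 7.2 grounds its incidence rate on this premise: "Since all positive cases are treated (and confirmed negative) at the end of" each year. A positive at the end of year K can then be read as an infection acquired in that year. The reinfection rate divides infections at the end of year K by the cohort members present at the end of both years "and positive at end of year K-1". It asks for neither treatment nor a later negative stool.

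Objective 2 in section 2.0 is: "Examine the efficacy of bovine chemotherapy on human infection and reinfection rates". Section 7.1 lists reinfection among the outcome measures, while the trial's end-point is human infection rates.

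Sections 3.1 and 5.2 prescribe a stool one month after treatment, re-treatment of positives, and repetition until cure. Section 5.2 says earlier studies "show 85% efficacy on a single praziquantel dose, with 100% efficacy following re-examination and re-treatment". Section 5.1 requires the one-month stool of cohort members treated "as part of the annual mass treatment or as a direct result of being egg positive", that is, of those who received treatment.

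The Appendix forms provide for exceptions. "FORM 2C Primary Individuals For Treatment" has a yes/no treatment field with reasons for no: "1= refused exam; 2= work outside area; 3=pregnant; 4=death; 5=other". Form 2D lists reasons for a missing follow-up stool: "refused 1 not at home 2 sick 3 others 4".

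**The concern.** The formula is right only if every positive at K-1 was cleared, and section 7.2 states that as fact instead of building it into the denominator. On Form 2C, pregnancy and the open category can apply to a known positive who stays in the village and so stays in the denominator. (A refused examination or a death cannot; work elsewhere can only if the absence is short.) An untreated positive has no required clearance stool. A treated member who gives no follow-up stool does not get the re-examination on which the 100% figure depends.

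An infection carried over from K-1 was not transmitted during year K, so bovine treatment cannot prevent it. At first follow-up it adds a similar amount to both arms and shrinks the relative difference. Because the denominator holds only prior positives, a small uncleared share matters more here than in overall incidence. The newly-infected rate leaves these members out. Reinfection could therefore look less responsive than new infection when the true effects are equal.

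**Working it through.** **Inputs from the Protocol.** Single-dose cure 85% (5.2), so 15% fail. Human prevalence 10-15% (4.1). Four pairs with 300 per village (7.3). Lowest effect row of the 7.3 table: 60% x 70% = 42%.

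**Assumptions, not in the documents.** Untreated share a = 1%. Share of the treated not retested m = 10% to 30%. Control reinfection r = 10%. Uncleared infections are still detected a year later, the uncleared share is equal in both arms, retested members end up cleared, and doses fail independently.

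**1. The plan's own figure.** Cure after k test-and-treat rounds = 1 - 0.15^k: 85.0%, 97.75%, 99.7%, 99.9%. This agrees with the stated 85% and, in effect, 100%. With full adherence nobody is left uncleared and the formula is unbiased.

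**2. Uncleared share.** u = a + (1 - a) x m x e, with e = 0.15 for one dose, or 0.15^2 = 0.0225 if positives are treated when found and again at mass treatment.

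**3. What the formula returns.** Observed rate = u + (1 - u) x r, with r = 10% in control and 0.58 x 10% = 5.8% in intervention.

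| Doses | m | u | Control | Intervention | Reduction shown |
|---|---|---|---|---|---|
| two | 10% | 1.22% | 11.10% | 6.95% | 37.4% |
| two | 30% | 1.67% | 11.50% | 7.37% | 35.9% |
| one | 10% | 2.48% | 12.24% | 8.14% | 33.5% |
| one | 30% | 5.46% | 14.91% | 10.94% | 26.6% |

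**4. Sensitivity.** With u = 2%, the reduction shown is 29.8%, 34.9% or 38.1% for control reinfection of 5%, 10% or 20%; with u = 5% it is 20.5%, 27.5% or 33.2%. If only half of uncleared infections are still detected, at r = 10%, u = 2% gives 38.1% and u = 5% gives 33.4%.

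**5. Overall incidence.** If 12.5% of the cohort (the midpoint of 10-15%) were positive at K-1, the carried-over share is 0.125 x u. At r = 10%, u = 1%, 2% or 5% gives 41.5%, 41.0% or 39.5% against a true 42%.

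**6. Precision.** Prior positives per arm at baseline: 4 x 300 x 10-15% = 120 to 180. With 150 per arm, 10% v 5.8% is about 15 v 8.7 events. The standard error of the log risk ratio is sqrt(1/15 - 1/150 + 1/8.7 - 1/150) = 0.41, so the 95% interval for the reduction runs from about 74% to -30%, before any allowance for clustering.

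**The case against.** The strongest reply is that the premise describes the prescribed procedure. Followed to the end, it clears everyone and the formula is unbiased; handling imperfect adherence is usually left to the statistical analysis plan. The first part stands. The second does not fully answer the point, because section 7.2 prints the formula and states clearance as fact, so an uncleared positive is counted by a stated rule. The exclusion of non-compliers in section 7.3 concerns the power calculation and does not alter these rates.

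The forms are also modest evidence. A field for reasons is routine, and the bovine treatment form (3D) carries the same five codes. They show that exceptions can be recorded, not that many are expected. The quoted premise stands under incidence, where the effect is slight; the reinfection paragraph relies on it only by implication.

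The size is uncertain. Sections 3.1 and 5.1 most plainly mean that positives are treated when found and again at mass treatment, which favours the smaller two-dose figures. A shift of five or six points is small beside the interval in step 6.

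A reader might go further and infer that the reinfection result could be mostly lost: with 10% uncleared, 42% would read as 20%, or as 13% at 5% control reinfection. The documents give no uncleared share, and 10% exceeds every scenario derived above.

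**Conclusion.** The point holds as a minor correction to a secondary outcome. The reinfection formula counts persistent infections as reinfections whenever a positive is left uncleared, and the protocol's own forms allow for that. At first follow-up the bias runs towards the null. With full adherence it is zero; under the assumed modest non-adherence a true 42% reduction reads as about 36% to 37% (two doses) or 27% to 33% (one dose). These figures depend on the assumed untreated and unretested shares, the assumed reinfection rate and persistence for a year.

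Two further inferences are not supported. One is that the trial's end-point is compromised: overall incidence moves by only a point or two in these scenarios. The other is that the formula could create a false benefit at first follow-up: an equal addition to both arms cannot. In later years positivity at K-1 is itself affected by the intervention, so an equal uncleared share in both arms can no longer be taken for granted.

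**What to change.** In section 7.2, leave out of both the numerator and the denominator of the reinfection rate any member known to be uncleared: untreated on Form 2C and not treated later, or still egg positive at the last follow-up stool on Form 2E. Report two versions beside it: one restricted to members with a documented negative post-treatment stool, and the present formula. Give the numbers of uncleared and unretested members by arm and village. Reword the premise to say that positives are to be treated and retested. Incidence can stay as it is.

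No extra field work is needed, since Forms 2C to 2E already record treatment, retest and result. If 1% are untreated, the main version loses 1 to 2 of the 120 to 180 baseline positives per arm. The confirmed-negative version loses more: 1% + 99% x 10% to 30% = 10.9% to 30.7%, or about 13 to 55. After year 1 the exclusion adds some conditioning on post-randomisation status, though the denominator already conditions on positivity at K-1; this is a reason to keep the present formula in the report.

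The main version keeps treated but unretested members, so some bias remains. With u = m x e at r = 10%, it shows 41.1% to 39.3% for two doses and 36.4% to 28.5% for one. The confirmed-negative version removes the rest, provided that a negative one-month stool means clearance; the documents give no test sensitivity.
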